### Statistical analysis

The analysis and reporting of the results will follow the CONSORT (Consolidated Standards of Reporting Trials) guidelines [44]. Descriptive statistics of socio-demographic, historical/lifetime trauma, sex- and drug-related HIV vulnerabilities, and health-related variables will be presented to assess comparability of the intervention and control groups. Mean (standard deviation) or median (quartiles) will be used for continuous variables and count (percentage) for categorical variables. Our primary analysis to evaluate the effect of the mHealth intervention on HIV prevention will be by intention to treat (ITT) for primary and secondary outcomes among all randomly assigned participants according to the study group to which they were originally allocated. Student’s *t* tests and chi-squared tests will be used to determine differences in the mean change in proportions or scores from baseline at 6 months or 1 year between the two study arms. If baseline characteristics are found to be substantially different between the two study arms, we will adjust for these factors by using regression models. In addition, we will conduct a secondary analysis by using a modified ITT approach including only participants who agreed to participate in the intervention making up the intervention group (excluding over-sampled participants who did not receive the intervention). To minimize the risk of bias introduced in our modified ITT analysis, we propose to use complier average causal effect (CACE) analysis [45]. This approach will allow us to retain the initial random assignment by taking into account two subgroups within the group pre-randomized to receive the intervention (those who did and did not actually receive the intervention) and then helping us to identify a similar subgroup of control participants who could have been expected to receive the intervention had it been offered [45]. By comparing expected and observed outcomes in these subgroups, we will obtain a less biased estimate of effect of the intervention [45]. Missing data will be approached by using multiple imputation. An up-to-date version of R statistical software will be used to conduct all analyses [46]. All tests will be two-sided; *P* values of less than 0.10 will be considered significant. We plan to conduct four predetermined exploratory subgroup analyses that may help to tailor the intervention for specific high-need populations, including comparisons by gender, city, injection drug use, and urban versus rural. Statistical methods similar to those described above for whole-group analyses will be conducted for primary and secondary outcomes. All subgroup results will be reported, regardless of significance. Inferences will be hypothesis-generating, given concerns related to multiple comparisons and lower power to detect an effect in subgroups.

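### The exploratory subgroup analyses use whole-group between-arm tests and name no arm-by-subgroup interaction test, so as worded they do not show whether effects differ (minor)

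*Protocol article*

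**What the plan says.** All of this stands in the Statistical analysis section of the protocol article.

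- **Purpose.** "We plan to conduct four predetermined exploratory subgroup analyses that may help to tailor the intervention for specific high-need populations".
- **Factors.** There are four: "including comparisons by gender, city, injection drug use, and urban versus rural".
- **Subgroup method.** "Statistical methods similar to those described above for whole-group analyses will be conducted for primary and secondary outcomes".
- **The whole-group methods referred to.** Change from baseline is compared arm against arm at each time point, by a t test for scores and a chi-squared test for proportions. Regression enters only conditionally: "If baseline characteristics are found to be substantially different between the two study arms, we will adjust for these factors by using regression models".
- **Level.** "All tests will be two-sided", with significance declared at P below 0.10.
- **Safeguards.** The article commits to reporting every subgroup result, significant or not, and adds: "Inferences will be hypothesis-generating, given concerns related to multiple comparisons and lower power to detect an effect in subgroups".

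No interaction or heterogeneity test appears anywhere in the article.

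**The concern.** To tailor an intervention one must know whether its effect differs between, say, women and men or Vancouver and Prince George. A between-arm test among women and another among men each ask whether that group's effect is zero. Neither asks whether the two effects differ. One result below 0.10 beside one above it can easily come from equal effects and halved sample sizes.

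At stake is how the subgroup results are read. A pattern of one significant and one non-significant subgroup invites the conclusion that the intervention works in one group only, and the method the article names gives no check on that conclusion.

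**Working it through.** **Inputs.** From the Sample size section: d = 0.40, one-sided 0.05, 80% power, 78 required per arm, about 20% attrition, target 100 per arm. From the Statistical analysis section: two-sided tests at 0.10. From the Intervention group section: 140 invitees, 70 per site, so city splits 50:50 in that arm. The article gives no split for the other factors. Equal halves are assumed for them, and uneven splits are shown below.

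**The plan's own figure.** n per arm = 2(1.645 + 0.842)² / 0.40² = 77.3, rounded up to 78 (normal approximation). The noncentral t gives 77.97. The stated 78 is reproduced. Two-sided 0.10 gives the same number. Allowing for attrition, 78 / 0.80 = 97.5, so 98, which the plan rounds to 100.

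**Power within one half.** With 78 analysed per arm, each half has 39 per arm. The noncentrality is 0.40 × √(39/2) = 1.77. Power at two-sided 0.10 is 54.2% by the noncentral t (54.8% by the normal approximation).

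**Chance that exactly one half is significant.** The halves are independent, so with equal effects and equal sizes the probability is 2p(1 − p):

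- 39 per arm per half: 2 × 0.542 × 0.458 = 49.6%
- 40 per arm per half: p = 55.1%, giving 49.5%
- 50 per arm per half (no attrition): p = 63.4%, giving 46.4%

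**Dependence on the true common effect** (39 per arm per half):

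| Common d | Exactly one half with P < 0.10 |
|---|---|
| 0 | 18% (2 × 0.10 × 0.90) |
| 0.2 | 35.1% |
| 0.3 | 46.7% |
| 0.4 | 49.6% |
| 0.5 | 41.5% |
| 0.6 | 27.3% |

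**Uneven splits** (assumed; d = 0.40, 78 per arm), using p₁(1 − p₂) + p₂(1 − p₁): 50.7% at 60:40, 53.9% at 70:30 and 59.0% at 80:20.

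**Diluted effect** (assumption: 40 of the 140 invitees go untreated, so d = 0.40 × 100/140 = 0.286): 49.6% with 140 and 100 analysed, and 47.7% with 112 and 80.

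**Interaction test at the same level.** In 40,000 simulated trials with two equal halves and equal effects, an interaction test at two-sided 0.10 declared a difference in 9.8% at d = 0.40 and 10.1% at d = 0. In the same simulations exactly one half was significant in 49.5% and 17.8%.

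**What the interaction test can detect.** With 39 per arm per half, the difference between the two subgroup effects has standard error √(4/39) = 0.320 in standard deviation units. For a true difference of 0.40, 0.40 / 0.320 = 1.25, and power at two-sided 0.10 is about 35% (normal approximation).

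**The case against.** The strongest reply is that the article does not rule out an interaction test. It says only that methods will be similar, it includes regression among the whole-group methods, and it speaks of comparisons by gender, city and so on. The source is a condensed article, and a separate analysis plan could add the term. The text also never says that a significant subgroup beside a non-significant one will be read as a difference. A reader might infer that it will; the documents do not support that as a statement of the plan. What remains is that the article names the kind of method to be used, and none of the whole-group methods it describes contains an arm-by-subgroup term.

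The safeguards also deserve weight. The factors are predetermined, all results will be reported, and the inferences are labelled hypothesis-generating. This limits the harm. But the reasons given for the label are multiplicity and low power, and neither supplies a test of difference.

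Three stronger readings are tempting and should be set aside:

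- **That equal effects will look different about half the time, without condition.** The figure holds near the planning effect. It falls to 18% if there is no effect and to 27% at d = 0.6 with equal halves.
- **That the programme would be withheld from some groups.** The article says only that the analyses "may help to tailor the intervention for specific high-need populations". Withholding is not mentioned.
- **That the number of subgroup tests is itself an unrecognised fault.** There are many, but the article already names multiple comparisons as a concern, and their number has no bearing on the absence of an interaction test.

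**Conclusion.** The point holds at minor severity. As worded, the subgroup analyses test each subgroup's effect against zero and do not address the question that tailoring raises. With equal halves and 78 analysed per arm, identical true effects produce one significant and one non-significant subgroup in about 50% of trials at d = 0.40, and in about 18% to 50% over d = 0 to 0.6. An interaction test at the same level errs in about 10%.

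This rests on reading the reference to whole-group methods as within-subgroup t and chi-squared tests. That is the natural reading but not the only possible one. It also rests on equal subgroup sizes, which the article documents only for city in the intervention arm. The primary intention-to-treat conclusion is not affected.

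**What to change.** State that effect modification will be judged by interaction. For each outcome analysed by subgroup, fit one regression on the whole sample with arm, subgroup, arm-by-subgroup interaction and the baseline value of the outcome. Report the interaction estimate with its confidence interval, and each subgroup's effect with its own interval. Add that differences between subgroups will not be inferred from significance within them. The list of outcomes need not change.

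The cost is a few sentences of analysis wording, with no change to data collection, sample size or conduct. The downside is wide intervals. With a standard error of 0.320, a 90% interval extends about 1.645 × 0.320 = 0.53 standard deviations either side, and power for a between-subgroup difference of 0.40 is only about 35%. A non-significant interaction must therefore not be read as proof of equal effects.

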
### Nested studies

#### Study implementation

As this study is the first of its kind in a community-based setting among young Indigenous people who use drugs, it is critical that the implementation of the intervention be described in detail. Daily mHealth memos prepared by each study site, combined with procedural documents, will inform a description of how a supportive two-way text-message program looks and functions in practice. Descriptive statistics generated from the mHealth baseline questionnaire will provide additional insight into the feasibility of applying this program in similar settings. The survey asks about ownership and use of mobile phones, how often participants text message, and perceived helpfulness or concerns about receiving text messages related to health.

#### Types of support requested

Examining the types of support requested by Cedar Project WelTel mHealth participants via text will help to identify current challenges accessing prevention services and support among young Indigenous people who use drugs. A comparative content analysis of text-message interactions captured on the WelTel platform over the study period will be used for this purpose. This descriptive analysis will help inform scale-up of this program, including the human resource requirements for future implementation in similar settings.

#### Participant perceptions

Participant perceptions of the mHealth intervention will be evaluated via the mHealth follow-up questionnaire. All intervention arm participants will be invited to complete an administered questionnaire to assess satisfaction with the care and support they received via the intervention. Evaluation of patient perceptions will include thematic analysis of narrative responses and basic descriptive statistics.

### Ethics

The Cedar Project follows the guidelines provided in the Tri-Council Policy Statement on Ethical Conduct for Research Involving Humans – Chapter Nine: Research involving the First Nations Inuit and Métis Peoples of Canada [47]. In addition, the study will adhere to the principles of Ownership, Control, Access and Possession in relation to research with Indigenous people [48]. Through the Cedar Project Partnership, Indigenous collaborators will continue to be involved in the conception, design and interpretation of the results of the Cedar Project WelTel mHealth study. The Cedar Project Partnership will serve as the data and safety monitoring board for this study. They have also approved this manuscript for publication. The Cedar Project WelTel mHealth study has been approved by the University of British Columbia Providence Health Care Research Ethics Board (H13-02718), and we will be accountable to them for approval and monitoring.

All participants have provided informed consent as part of the main Cedar Project cohort study. Participants randomly assigned to receive an invitation to participate in the Cedar Project WelTel mHealth intervention will undergo an additional consent process. After the study participant is invited to participate in the Cedar Project WelTel mHealth study, a trained Cedar Project staff member will describe the study. If the person would like to enroll, the research staff will review the consent form and answer any questions. Participants who give consent are provided with a copy of the study introduction letter and consent form.

### Harms

Adverse events will be documented in writing and reported to investigators. Study staff at both sites have been trained in recognizing and reporting of adverse events, including those directly attributable to the intervention (e.g., accidental disclosure of illicit drug use) and those resulting from trial participation. Because the study takes place in a community-based (not clinical) setting, staff will make referrals to care where appropriate. Potential harms will be outlined to participants during the informed consent process. All unanticipated risks to human participants or others will be reported to the Cedar Project Partnership and the University of British Columbia/Providence Health Care Research Ethics Board where appropriate.

### Dissemination

Knowledge translation is a hallmark of the Cedar Project and will be a key component of the Cedar Project WelTel mHealth study. Integrated knowledge translation is planned throughout the study, and updates will be provided to the Cedar Project Partnership at quarterly meetings. Findings will be shared through ceremony with Indigenous partners; peer-reviewed publications and presentations; and consultations with policy makers and service delivery organizations to support uptake of results.

## Discussion

Innovative, culturally safe interventions that address the barriers to HIV prevention while supporting the strength of young Indigenous people who use drugs are urgently needed. This study, due to report its findings in 2017, tests the effectiveness of a two-way supportive text-message program delivered in a community-based setting to support HIV prevention among young Indigenous people who use drugs. Despite presenting a tremendous opportunity to connect young, highly transient Indigenous people who use drugs to prevention services and support, supportive two-way mHealth programs have yet to be tested for HIV prevention in a community-based setting with young Indigenous people who use drugs [34, 49–51].

Other researchers have used two-way supportive messaging interventions to engage people living with HIV in care and to improve adherence [34, 36, 40, 52, 53]. Recent randomized controlled trials in Kenya indicated that introducing mobile-phone technology into HIV case management improved HIV treatment adherence and HIV-related clinical outcomes, despite high levels of poverty, remote and rural living, transience, stigma, and discrimination [34, 50, 54]. These studies have demonstrated the importance of text-message programs that are both supportive and interactive [35, 55–57], as passive mHealth programs that seek to monitor, remind or educate have had limited success [58–60]. It is important to note that we have deliberately chosen an open-ended weekly text message to allow participants to set their own priorities around their health and well-being, as well as to avoid possible disclosure of drug use and other sensitive issues.

We have chosen a cohort-embedded Zelen pre-randomized controlled trial design [61–63]. Our ongoing Cedar Project cohort study provides the opportunity to support recruitment into the embedded trial and also allows us to use routinely measured outcomes collected longitudinally among the whole cohort. All participants entering the cohort have consented to providing observational data. Consent to “try” the intervention is being sought only from those who have been pre-randomized to receive the intervention [63]. Study outcomes among randomly selected participants will be compared with those of the cohort members not randomly selected to receive the intervention. Another advantage of this design is to minimize false hopes, resentment, and contamination among controls had they learned they were not receiving a potentially valued intervention through trial consent and randomization [61, 62]. In our instance, as it is not possible to completely separate intervention participants from the rest of the cohort, it is likely that some members of the cohort will come to know about the intervention. However, even if control participants have or obtain a phone and cellular plan, full crossover of participants from control to intervention is not possible, owing to the nature of the intervention. As noted above, neither group will be aware of the hypotheses under study. A limitation of this design is that a significant number of participants allocated to the intervention arm may refuse to receive it whereas control subjects do not have this option. Including the former group in an ITT analysis may dilute the treatment effect, whereas excluding them could lead to a biased comparison. In our case, we believe that the intervention is likely to be highly valued among invitees and there will be few who refuse. Nevertheless, this will be monitored closely, and as noted earlier, we will also use a modified ITT approach.

A key component of the Cedar Project WelTel mHealth study is relational accountability [64]. We honour our relationships with study participants who have continued to share their stories with us since joining the Cedar Project. Testing this intervention is a way for us to respond to the clear message from Cedar Project participants about the importance of having support to navigate barriers to care and services that they face in their daily lives. An additional component of our relational accountability is through the governing leadership of the Cedar Project Partnership, who work to ensure that this research is relevant to the communities they represent and is conducted in a good way.

### Limitations

Our decision to over-sample in the intervention arm to adjust for refusals to participate or difficulty locating participants may result in a dilution of the effect of the intervention in ITT analysis. As a result, we have proposed a parallel, modified ITT analysis, which may be affected by selection bias. Diversity of HIV risk among participants (non-homogeneity) may also dilute the detected effect of the intervention. Representativeness of the sample is dependent on representativeness of the Cedar Project cohort study sample overall; however, we have made a considerable attempt to ensure that the sample represents the population under study [12]. As this study involves a package of support that includes mobile phones, two-way text messaging, and support, it is difficult to determine the relative contribution of components of the package to any effect the intervention may have. The qualitative nested studies will help in this regard. Furthermore, we cannot rule out that simultaneous co-interventions could impact our results. As BC’s HIV incidence has been stable for several years and many public health initiatives (including needle exchanges and safe injection sites) are already in place, we feel it is unlikely that new transformative co-interventions will take effect over the study period. However, we will monitor potential co-interventions that could impact study outcomes through our main cohort questionnaires, as well as track major policy and programmatic changes in the Province. Blinding in this study is not possible as assessors have strong relationships with participants. In addition, loss to follow-up may be higher in the comparison group than the intervention group. Cedar Project participants are highly transient and often difficult to track down [41]. Having a mobile phone and consistent airtime will likely make it easier to reach participants receiving the intervention for follow-up visits. Active follow-up with all participants through phone, email, and outreach will help ensure retention and interview appointment attendance. In addition, our measures may not adequately capture complex concepts such as connection to culture and resilience. Finally, the intervention under study is complex and multifaceted. It may be that our proposed outcomes do not adequately capture the impact of the intervention on the lives of participants involved.

### Trial status

Enrollment in the trial has begun but has not yet reached full enrollment.

## Abbreviations

BC: British Columbia
CD-RISC: Connor-Davidson resilience scale
ITT: Intention to treat
mHealth: Health care delivered via mobile phone
NX: Needle exchange
OST: Opioid substitution therapy
SIF: Safe injection facility
SCL-90-R: Symptom checklist 90-R
